#### Inclusion criteria:

- birth weight < 1500g
- less than 24 hours of age
- requiring intensive care and in whom it is considered appropriate to continue intensive care
- written informed parental consent

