#### Exclusion criteria

- maternal diabetes including gestational diabetes
- babies where the appropriateness of continuing intensive care is being discussed
- major congenital anomalies

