## **Sample size consideration**

Bolt et al [56] studied growth and body composition in 15 SGA and 26 AGA preterm born infants during the first 2 years of life. They found that growth expressed as anthropometry according to Dauncey [57], IGF-1 and IGFBP-3 were significantly lower in SGA than in AGA infants ( $p < 0.01$ ). Catch up growth during the first year of life was significantly higher in SGA infants compared to AGA infants ( $p < 0.01$ ).

In addition, growth and body composition was studied in 14 preterm infants with chronic lung disease and treated with corticosteroids to facilitate weaning from

the ventilator and 18 preterm controls during the first 2 years of life [58]. Body composition at term and 3 months corrected age in preterm infants treated with dexamethasone for chronic lung disease, who received extra caloric intake until term age, did not differ from preterm infants without CLD.

Based on the results of both studies in combination with power calculation it is expected that groups of 30 fully evaluable subjects (insulin treated vs. controls) will be sufficient to detect a difference of 0.5 SDS in growth parameters with a power of 80% at  $\alpha=0.05$ .

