### **Statistical analysis**

Results are presented as mean  $\pm$  standard deviation. We will compare the results of infants treated with insulin to those receiving standard care on an intention to treat basis and within each group we will also compare the results of SGA infants to AGA infants.

Comparison between the groups on all different time points will be analysed using the unpaired t-test.

Within group differences between different time points and differences between the groups in the changes of the values in time will be analysed with repeated measures analysis of variance (ANOVA).

A p value of  $<0.05$  will be considered as statistically significant

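### The fixed unpaired t-test ignores sibling correlation although twins and triplets may enter; a pregnancy-level mixed model is a cheap, minor improvement

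*Protocol*

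**What the plan says.** The Statistical analysis section of the protocol fixes the between-arm test: "Comparison between the groups on all different time points will be analysed using the unpaired t-test". Changes over time go to repeated measures ANOVA, and SGA infants are compared with AGA infants within each arm. The threshold is given as "A p value of $<0.05$ will be considered as statistically significant". No term for mother, pregnancy or family appears.

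Entry is by "birth weight < 1500g", age under 24 hours, need for intensive care and parental consent. The exclusions are maternal diabetes, doubt about continuing intensive care, and "major congenital anomalies". Neither list mentions multiple birth, so twins and triplets are eligible by omission.

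On allocation, the two summary tables and the short account of the parent trial under Measurements of outcomes speak of randomising infants who meet the criteria. None says whether siblings go together, apart or independently. The sample size of 30 evaluable infants per arm has no allowance for siblings.

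**The concern.** Siblings share a mother, a pregnancy and a gestational age, so growth SDS, hormone levels and development are likely to be more alike within a sibling set than between sets. An unpaired t-test takes its standard error as if all 60 infants were unrelated. If siblings share an arm, that standard error is too small and the trial declares differences too often. If siblings are in opposite arms, it is too large, and the precision of a within-pair contrast is thrown away.

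With only 60 infants, a few sibling sets can matter, and power is already short. The correction also needs a link between siblings in the data, which may be hard to rebuild later if it is not recorded.

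**Working it through.** **The plan's own figure.** The protocol says that 30 evaluable infants per arm are "sufficient to detect a difference of 0.5 SDS in growth parameters" "with a power of 80% at" a significance level of 0.05. With SD 1 and a two-sided test, n per arm = 2 × (1.96 + 0.84)² / 0.5² = 62.8, so 63, not 30. With 30 per arm the power is about 48% (t distribution). The stated figure is reached only with an SD of about 0.68, which the protocol does not give. This is a separate and larger problem that siblings do not explain. It fixes the reference effect used here: 0.5 / 0.68 is roughly 0.73 SD, at which 30 per arm gives the t-test about 79-80% power.

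**Inputs.** From the protocol: 30 per arm, unpaired t-test, threshold 0.05 (taken as two-sided). Assumed, because the protocol gives neither: share of infants from twin pairs s = 0.2 to 0.4 (6 to 12 pairs among 60), and sibling correlation ρ = 0.3 to 0.7.

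**Variance of the arm difference.** Relative to independence, the ratio is 1 + ρ × (pairs in the same arm − pairs in opposite arms) / 30. With all pairs together it is 1 + sρ; with all pairs apart it is 1 − sρ. The false-positive rate of the t-test is then about 2 × [1 − Φ(1.96 / √ratio)].

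| s | ρ | Together: ratio | Together: rate | Apart: ratio | Apart: rate |
|---|---|---|---|---|---|
| 0.2 | 0.3 | 1.06 | 5.7% | 0.94 | 4.3% |
| 0.2 | 0.5 | 1.10 | 6.2% | 0.90 | 3.9% |
| 0.4 | 0.5 | 1.20 | 7.4% | 0.80 | 2.8% |
| 0.4 | 0.7 | 1.28 | 8.3% | 0.72 | 2.1% |

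Simulation with 40,000 trials per cell agrees: 5.7% to 8.6% together and 4.2% to 2.1% apart. With siblings together, 30 per arm would have to become 32 (30 × 1.06) to 39 (30 × 1.28) to keep the same information.

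**Individual randomisation.** In a 30:30 split a given pair lands in the same arm with probability 29/59 and in opposite arms with probability 30/59. The expected ratio is therefore 1 − sρ/59, which is 0.995 even at s = 0.4 and ρ = 0.7. Simulated false-positive rates are 4.8% to 5.2%.

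**Power under individual randomisation, at 0.73 SD.**
- t-test: about 79-80%.
- Model that knows ρ = 0.5 exactly: 82%, 83% and 84% at 20%, 30% and 40% twins; 90% at 40% twins with ρ = 0.7. These are upper bounds, since a real analysis must estimate ρ.
- Fitted mixed model (REML) with ordinary 58 degrees of freedom: about 6-7% false positives, so its apparent power is not usable.
- The same model with Kenward-Roger: 5.1-5.8% false positives. The gain is about 0-2 power points at ρ = 0.5 and about 8 at 40% twins with ρ = 0.7. At a low twin share it gains nothing or loses about one point.

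**If siblings share an arm.** In a simulation of the fitted model at ρ = 0.5 to 0.7, the t-test gave 6.4-7.7% false positives and the Kenward-Roger model about 5%.

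**The case against.** The strongest reply is that the text speaks of randomising infants and nothing suggests allocation by pregnancy. On that reading the t-test holds its error rate on average, and the inflation needs a rule found nowhere in the protocol. This stands. A reader might infer that the test is wrong whichever way siblings are allocated, or that false positives will be inflated. The documents support neither: the allocation rule is simply not stated, and under individual randomisation the t-test is valid on average.

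It is also fair that the power gain looks larger than it is when the sibling correlation is treated as known, and that a carelessly fitted mixed model adds false positives where the t-test had none. Both points stand, and they determine the form of the fix.

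Third, the parent trial is described only briefly, and its protocol or a statistical analysis plan may settle sibling allocation and clustering. That lowers the priority. It does not remove the point, because this protocol names the test itself, and as written that test has no family term.

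Finally, individual randomisation does not protect the SGA versus AGA comparison. It is not a randomised contrast, so where siblings in one arm share SGA or AGA status, nothing cancels on average.

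**Conclusion.** The point holds as a minor, cheap improvement. The protocol fixes a test that ignores sibling correlation in a population where siblings may enter, and it leaves open the allocation rule that decides the consequence: about 6-9% false positives with siblings together, about 5% with individual randomisation, and about 2-4% with siblings forced apart. These figures rest on assumed twin shares of 20-40% and correlations of 0.3-0.7. Fewer siblings or a weaker correlation would shrink them towards 5%. That siblings will enter at all is likely, but it is inferred from the silence of the eligibility lists. The case for changing the test is that it protects the error rate if siblings share an arm and costs almost nothing if they do not. A large gain in power should not be expected.

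**What to change.** 1. Record a mother (pregnancy) identifier for every infant.
2. State how the parent trial allocates siblings: together, apart or individually.
3. Replace the unpaired t-test for growth SDS and the other continuous outcomes by a linear mixed model with arm as fixed effect, pregnancy as random effect and the Kenward-Roger correction. Uncorrected degrees of freedom should not be used.
4. Put the same random effect in the over-time analysis and in the SGA versus AGA comparison.

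With no siblings in the data the model reduces to the t-test. The cost is a few lines of analysis text and one data field. The downside is small: the sibling correlation is estimated imprecisely from few sets, and at a low twin share the model may lose about one power point.

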## **Measurement of outcomes amendment**

Growth and body composition

- Anthropometry according to Dauncey et al. [57] on day 7, at 32 weeks postmenstrual age, at expected date of delivery (40 weeks) and at the corrected age of three, six, twelve and twenty-four months.

Measurements include naked body weight (measured on a electronic scale to the nearest 5 g), crown-heel length (measured on a length board to nearest 1 mm) and head circumference (using a measuring tape to the nearest 1 mm). Crown-back length and bilateral lengths of the upper arms, lower arms and lower legs are measured (total length). In addition, chest circumference, bilateral circumferences of the upper arms, thighs and calves (total circumference) and bilateral skin-fold thickness at four sites (subscapular, abdominal, triceps and biceps) are measured.

- quantitative ultrasound of the second metacarpus [59] for assessment of bone mineral status on day 7, at 32 weeks postmenstrual age, at expected date of delivery (40 weeks) and at the corrected age of three, six, twelve and twenty-four months
- IGFBP-3 on day 7 and 28 and IGF-1, IGFBP-1 and IGFBP-3 in serum at the corrected age of 6 and 24 months

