## 5. Gonadotrophins and steroids

- gonadotrophin (FSH and LH) measurements in urine on day 7 and 28, at 32 weeks postmenstrual age, at expected date of delivery (40 weeks) and at the corrected age of three months. As shown by Kuijper et al. urinary gonadotrophin levels are a proper reflection of the serum levels [61].
- oestrogens and androgens in urine on day 7 and 28, at 32 weeks postmenstrual age, at expected date of delivery (40 weeks) and at the corrected age of three months

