## **Ethical considerations**

Taken the blood samples of the first project into account only at the corrected age of 6 and 24 months extra blood samples (total amount 1 ml) will be taken. These samples have to be taken prior to feeding. The sample size at the age of 7 days and 28 days for the first project will be increased with 250 µl; these blood samples are taken from the arterial line. Insertion of a central venous and arterial line in these very low birth weight infants is part of routine care. Taken the urine sample of the first project into account, 4 extra urine samples (5 ml) will be taken on day 28, at 32 weeks postmenstrual age and at the corrected age of 0 and 3 months. The sample size at the postnatal age of 7 days will be

increased with 5 ml. All urine samples are collected in a pediatric urine collection pouch.

It is important to notice that in this project most determinations in blood and urine are accomplished in samples that are already collected for clinical reasons; the remaining material is stored and used for analysis within this project.

Anthropometry and quantitative ultrasound will be performed on day 7, at 32 weeks postmenstrual age and at the corrected age of 0, 3, 6, 12 and 24 months. During hospitalisation this will be combined with routine nursing care to minimize the burden.

Saliva samples will be collected at the corrected age of 6 and 24 months.

Data of each subject will be stored in a case record form (CRF) and into a computer file for analysis. Patient data, blood, urine and saliva samples will be anonymised. After analysis, the data will be used for scientific presentations and publications in scientific journals. All data will be reported anonymously.

Unexpected findings will be reported to the pediatrician and the general practitioner in writing. The subjects will be insured according to the research insurance policy of the VU University medical center (see appendices).

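### Repeated-measures ANOVA with the 32-week visit as a level would leave out infants born after 32 weeks, whom the entry criteria admit

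*Protocol*

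**What the plan says.** **Method.** The Protocol's Statistical analysis section uses unpaired t-tests at each time point. Repeated-measures ANOVA is reserved for "Within group differences between different time points" and for the comparison between arms of change over time. The comparison of insulin with standard care is to be made "on an intention to treat basis". The section does not list the time points that enter the ANOVA.

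**Eligibility.** The Inclusion criteria require "birth weight < 1500g", age under 24 hours, need for intensive care, and consent. The Exclusion criteria cover maternal diabetes, doubt about continuing intensive care, and "major congenital anomalies". Neither list mentions gestational age.

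**Schedule.** Under Measurement of outcomes amendment, anthropometry and bone ultrasound are placed "on day 7, at 32 weeks postmenstrual age, at expected date of delivery (40 weeks") and then at corrected ages 3, 6, 12 and 24 months. Ethical considerations repeats this: "Anthropometry and quantitative ultrasound will be performed on day 7, at 32 weeks postmenstrual age and at the corrected age of 0". Under Gonadotrophins and steroids, urine is collected "on day 7 and 28, at 32 weeks postmenstrual age, at expected date of delivery (40 weeks") and at 3 months corrected age. The Measurements table lists 32 weeks after day 7 and day 28 for everyone. No rule covers an infant who is already past 32 weeks at birth.

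**The concern.** The schedule mixes two clocks: days since birth (day 7, day 28) and postmenstrual age (32 and 40 weeks, then corrected age). With entry by weight alone, gestation at birth can vary widely. An infant born after 32 weeks has no 32-week visit to attend, and in others that visit comes before or after the postnatal ones depending on maturity.

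Classical repeated-measures ANOVA needs a value at every level of the time factor from every infant. If 32 weeks is a level, the infants left out are selected by maturity. The longitudinal result would then describe a narrower group than the one randomised. This affects growth and catch-up growth, which are part of the primary objective.

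**Working it through.** The plan gives no figure on this point to reproduce. The check sets the visit schedule against the entry criteria.

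**Inputs.** Entry criteria, visit times and method are as set out above. Gestational age at birth (GA) is in weeks. I take day 7 and day 28 as 7 and 28 days after birth; counting the day of birth as day 1 would move the day-7 and day-28 thresholds below by one day.

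**Step 1: when the 32-week visit falls.** Postnatal day of the visit = (32 − GA) × 7.

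| GA at birth | Postnatal day of 32-week visit | Relative to day 7 | Relative to day 28 (urine only) |
|---|---|---|---|
| 24 | 8 × 7 = 56 | 49 days after | 28 days after |
| 26 | 6 × 7 = 42 | 35 days after | 14 days after |
| 28 | 4 × 7 = 28 | 21 days after | same day |
| 30 | 2 × 7 = 14 | 7 days after | 14 days before |
| 31 | 1 × 7 = 7 | same day | 21 days before |
| 32 | 0 (day of birth) | 7 days before | 28 days before |
| 33 | −7 | visit cannot exist | visit cannot exist |

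**Step 2: thresholds.**
- The visit exists only if (32 − GA) × 7 ≥ 0, that is GA ≤ 32+0.
- It falls on or before day 7 if (32 − GA) × 7 ≤ 7, that is GA ≥ 31+0. Between 31+0 and 32+0 it therefore falls within the infusion week.
- It falls on or before day 28 if GA ≥ 28+0. This matters for urine only, because anthropometry and ultrasound have no day-28 visit.

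**Step 3: which outcomes are touched.**
- Anthropometry and ultrasound: 7 visits. Six remain without 32 weeks. Five (term, 3, 6, 12 and 24 months) lie on the corrected-age scale, in the same order for every infant.
- Urine gonadotrophins and steroids: 5 visits. Four remain without 32 weeks. Two (term and 3 months) lie on the corrected-age scale.
- HOMA insulin sensitivity, DHEAS, salivary cortisol and neurodevelopment: no 32-week visit.

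**Step 4: how many infants.** The Protocol gives no gestational-age distribution. If a share p of the 60 infants were born after 32 weeks, 60 × (1 − p) could have the visit. For assumed values of p of 5, 10, 20 and 30%, that is 57, 54, 48 and 42. These are illustrations, not estimates.

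**Step 5: is the treatment comparison biased?** Gestational age is fixed before randomisation, so exclusion on it does not differ by arm in expectation. With the same effect in all infants, the reduced and full analyses estimate the same quantity. If, purely as an illustration, the effect were 0.5 SDS in infants who can have the visit and zero in the rest, the effect over all infants would be 0.5 × (1 − p) = 0.475, 0.45, 0.40 and 0.35 for the four values of p. The reduced analysis would still target 0.50. The population changes; the comparison within it remains randomised.

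**The case against.** The case against is substantial. The Protocol does not say that 32 weeks is a level of the ANOVA. Its primary objective is framed on corrected age, where five of the seven anthropometry visits line up for everyone. A reader might infer that the ANOVA cannot be carried out at all, but it can be run without the 32-week level.

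A reader might also infer that differing visit order removes infants. It removes none: it only changes what a step from one visit to the next means, and for anthropometry the order is day 7 then 32 weeks for every infant born before 31+0.

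The t-tests do not need complete series, so all available infants can enter them. The words complete case do not appear, and the handling of missed visits may be in a statistical analysis plan that is not shown.

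All of that stands as a limit on the point. It does not remove it. The Protocol itself fixes the method, the schedule, the entry criteria and the intention-to-treat claim, and these do not fit together for infants born after 32 weeks. Dropping the 32-week level would be a repair that the text does not state, and it would discard measurements from the infants who do have the visit.

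**Conclusion.** The point holds in a limited form. If the 32-week visit is a level, the named method excludes eligible infants by maturity, together with any infant who misses another included visit. That fits poorly with an intention-to-treat analysis of change over time. The affected outcomes are anthropometry, bone ultrasound and urine hormones.

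The conclusion rests on two readings: that the ANOVA is the classical form needing complete series, and that all scheduled visits enter it. The text suggests both but states neither.

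Three stronger readings go beyond the documents. One is that the randomised contrast is biased; exclusion on a baseline factor need not do that. Another is that a specific loss of power follows; no gestational-age distribution or rate of missed visits is given from which to derive one. The third is that those left out are mostly small for gestational age; this is plausible under a weight limit, but no figure supports it. The size of the problem is therefore unknown, and could be small.

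**What to change.** In the Statistical analysis section, replace repeated-measures ANOVA by a linear mixed model that:
- uses all available measurements from all randomised infants;
- takes actual postmenstrual (corrected) age as the time scale, with postnatal age for the day-7 and day-28 samples;
- reports treatment contrasts at the common corrected-age visits: term, 3, 6, 12 and 24 months, where the outcome is measured.

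State that no 32-week value is required from infants born at or past that age. A 32-week measurement in an infant born between 31+0 and 32+0 is kept and enters at its actual age.

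The cost is slightly more modelling and a change of wording; no new data or visits are needed. The model assumes that missed visits are missing at random given the data in the model, and this should be stated.

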## **Aims of the study**

In the main multi-centre study 500 preterm infants will be randomised to receive either a continuous infusion of insulin for the first 7 days of life, or receive standard neonatal care. Aims of this amendment study are to investigate in a subpopulation of 60 preterms the effect of this early insulin replacement on growth and body composition, insulin sensitivity, the function of the HPA-axis and HPG-axis and neuro-motor development in infancy and during early childhood.

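### The analysis of change in growth starts at the end of the infusion (day 7) and misses any effect already present; birth-weight SDS should be the starting point for weight and a covariate throughout

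*Protocol*

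**What the plan says.** **Treatment window.** Infants in the insulin arm receive "a continuous infusion of insulin for the first 7 days of life" (Aims of the study).

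**Growth visits.** Anthropometry and bone ultrasound are scheduled "on day 7, at 32 weeks postmenstrual age, at expected date of delivery (40 weeks) and at the corrected age of three, six", then 12 and 24 months (Measurement of outcomes amendment). Ethical considerations and the Measurements table give the same schedule. No study measurement of growth at birth or on day 1 is listed.

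**Analysis.** The Statistical analysis section sets two between-arm methods. For values: "Comparison between the groups on all different time points will be analysed using the unpaired t-test". For change: "differences between the groups in the changes of the values in time will be analysed with repeated measures analysis of variance". Neither names a baseline or a covariate. Birth size enters only through a comparison of SGA with AGA infants inside each arm.

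**Objective.** The primary objective is growth, catch-up growth and body composition over the first two years of corrected age.

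**Birth weight.** It is an inclusion criterion ("birth weight < 1500g"), so it is known for every infant.

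**The concern.** The Rationale places the intended anabolic action of insulin in the first week, and the Hypothesis expects better weight gain. The first growth value in the scheduled series is taken when that week is over. It is therefore already an outcome of treatment, yet an analysis of change over the scheduled visits uses it as its start.

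A group-by-time test asks whether the two mean profiles are parallel. If insulin infants are ahead by day 7 and stay ahead by the same amount, the profiles are parallel and the test has nothing to find. If the lead shrinks later, the test finds a difference in the direction of slower growth on insulin, even though insulin infants were never smaller. Catch-up growth is itself a change, and this is the only planned method that compares change between the arms.

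Birth size is also left out of every between-arm comparison. The cohort cited under Sample size consideration (15 SGA and 26 AGA preterm infants) showed lower growth and higher catch-up in SGA infants, each with p<0.01. Birth size is thus prognostic on the protocol's own evidence. At 30 per arm, leaving it out costs precision.

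**Working it through.** **Inputs from the protocol.** 30 fully evaluable infants per arm, target difference 0.5 SDS, power 80%, α = 0.05 (Sample size consideration); seven growth visits.

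**Assumptions.** Two-sided test. SD of the growth SDS between 0.69 and 1.0. Correlation r of the starting value with the later SDS: 0.5 or 0.7. The protocol states none of these.

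**1. The plan's own figure.** By the normal approximation, the SD that gives 80% power with 30 per arm is 0.5 / [(1.960 + 0.842) × √(2/30)] = 0.69. With SD = 1, the reference SD of an SDS, 63 per arm are needed (64 by the t-test). The stated 30 is therefore reproduced only with an SD of about 0.69, so both values are carried below. Power in steps 2 and 4 is by the t-test.

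**2. What change from day 7 retains.** If a fraction f of the 0.5 SDS effect is present at day 7 and the full effect is present later, the difference in change is 0.5 × (1 − f). The SD of the change is SD × √(2(1 − r)). With r = 0.7 this is 0.53 (SD 0.69) or 0.77 (SD 1).

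| f | difference in change | power, SD 0.69 | power, SD 1 |
|---|---|---|---|
| 0 | 0.500 | 0.95 | 0.69 |
| 0.25 | 0.375 | 0.76 | 0.45 |
| 0.5 | 0.250 | 0.43 | 0.23 |
| 1 | 0 | 0.05 (error level) | 0.05 (error level) |

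If instead a 0.5 SDS lead at day 7 fades to zero, the difference in change is 0 − 0.5 = −0.5 SDS, against insulin.

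**3. The seven-visit test itself.** Simulated group-by-time F-test: 30 per arm, equal correlation 0.7 between visits, 4,000 runs per case. The final effect is 0.5 SDS in each case.

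| Course of the effect | Group-by-time, SD 0.69 | Group-by-time, SD 1 | t-test at last visit, SD 0.69 | t-test at last visit, SD 1 |
|---|---|---|---|---|
| Complete at day 7, then kept | 0.06 | 0.05 | 0.81 | 0.48 |
| Half present at day 7 | 0.39 | 0.19 | 0.79 | 0.48 |
| Arises wholly after day 7 | 0.97 | 0.71 | 0.79 | 0.48 |

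The group-by-time test depends on when the effect arises. The t-test at the last visit does not.

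**4. Gain from adjusting for birth-weight SDS.** The residual SD is SD × √(1 − r²), and the full 0.5 SDS stays in the contrast.

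| r with birth-weight SDS | residual SD (SD 0.69) | power | residual SD (SD 1) | power |
|---|---|---|---|---|
| 0 (unadjusted) | 0.690 | 0.79 | 1.000 | 0.48 |
| 0.5 | 0.598 | 0.89 | 0.866 | 0.59 |
| 0.7 | 0.493 | 0.97 | 0.714 | 0.76 |

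**The case against.** - **The t-tests keep the effect.** A reader might infer that the plan as a whole removes the effect under study. It does not. The t-tests subtract nothing, include day 7 as an outcome and are unbiased under randomisation. A lasting early gain would show at every visit, and a gain that is lost would show as an early difference that fades. This stands, and it limits the weight of the point. It does not repair the change analysis, and the section does not say which result prevails if the two methods disagree.
- **Day 7 is not named as the reference.** True: the day-7 start follows from the visit schedule, and birth weight is not ruled out as a first value. A baseline can also be left to a statistical analysis plan. But the section does fix the methods, and as they stand, on the listed visits, the first growth value is on day 7.
- **Later effects are retained.** True. The Rationale says that birth weight is often not regained for several weeks, and the objective covers two years. Only the share present by day 7 is lost. IGF-1 and IGFBP-1 have day-1 samples in the main study, so the point concerns growth and body composition.
- **A repeated measures ANOVA also has a group main effect.** It would detect a constant shift (simulated power 0.90 with SD 0.69, 0.60 with SD 1). The section, however, assigns the ANOVA to differences within groups over time and to differences in change.
- **Birth-weight SDS is not listed as collected.** A reader might assume that it is, but the protocol mentions it only when describing a cited study. It has to be derived. No skinfold or bone ultrasound value at birth is scheduled.
- **Adjustment is a refinement.** Fair. It improves precision and deals with chance imbalance; it corrects no bias in the t-tests.

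**Conclusion.** The point holds in a limited form. On the scheduled visits, the repeated measures analysis of change misses the part of any growth effect present at day 7. It has no power for an effect complete by then and kept, and it would point against insulin if an early gain faded. How much is lost depends on how much of the effect arises in the first week, which the documents do not quantify. The visit-by-visit t-tests remain valid, so the trial can still show a growth difference. What the plan lacks is a sound between-arm comparison of catch-up and any use of birth size between arms.

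The zero for an effect that is complete and kept needs no assumed SD or correlation. The power gains from adjustment do: 0.11 to 0.28 if the SD is 1 (0.59 − 0.48; 0.76 − 0.48), and 0.10 to 0.18 if it is 0.69 (0.89 − 0.79; 0.97 − 0.79), for r of 0.5 to 0.7. This is a worthwhile improvement, short of a defect that must be corrected before the trial can proceed.

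**What to change.** Amend the Statistical analysis section as follows:

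1. Derive birth-weight SDS for every infant from birth weight, gestational age and sex, and name the growth reference used.
2. For weight, take birth-weight SDS as the pre-treatment starting point and define weight catch-up as change from it.
3. Treat day 7 as the first outcome visit, not as a baseline.
4. Replace the unpaired t-tests for growth and the comparison of change by ANCOVA at each visit, or one mixed model over all visits, with birth-weight SDS as covariate. For weight, the adjusted arm difference is the same whether the outcome is attained SDS or change from birth SDS, so one analysis serves both growth and catch-up.
5. For length, head circumference, skinfolds and bone ultrasound, where no birth value is listed, use birth-weight SDS only as a prognostic covariate and report arm differences at each visit, not change from day 7 as a treatment effect.

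The cost is wording and one derived variable. No visit, sample or measurement is added: birth weight is recorded for eligibility, and the SGA/AGA split already needs it relative to gestational age.
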